Each subject will be instructed to complete a diary card, to describe any symptoms experienced following the study vaccine. All adverse events and local and systemic reactions must be reported and documented. The period of observation for adverse events extends from the time the subject gives informed consent until he or she undergoes the final study examination. This may include a period before and after an active treatment of an investigational product (study vaccine) or other medication.

The Investigator will monitor all adverse events, regardless of severity, until resolution or stabilisation. All subjects experiencing adverse events - whether considered associated with the use of the study vaccine or not - must be monitored until symptoms subside and any abnormal laboratory values have returned to baseline, or until there is a satisfactory explanation for the changes observed, or until death, in which case a full pathologist's report should be supplied, if possible. All findings must be reported on an “Adverse Events” CRF and on the “Vaccine Serious Adverse Event” form, if necessary, which is part of the Investigator’s study file. All findings in subjects experiencing adverse events must be reported also in the subject's medical records.

In addition, any event resulting in a subject’s withdrawal from subsequent vaccinations or from follow-up should be reported according to the protocol instructions. All serious adverse events which occur during the course of the trial, whether considered to be associated with the study vaccination or not, have to be reported **within 24 hours** or at the latest on the following working day by telephone or fax to the Sponsor.

As far as possible, all points raised on the “Vaccine Serious Adverse Event” form need to be addressed and faxed immediately to the Monitor of the Sponsor. The event must also be documented on the “Adverse Events” CRF.

After receipt of the initial report, the Monitor will review the information and contact the Investigator if it is necessary to obtain further information for assessment of the event. Any medication or other therapeutic measures used to treat the event will be recorded on the appropriate CRF(s) in addition to the outcome of the AE.

Any urgent safety measure to protect trial subjects against any immediate hazard to their health or safety and any SUSARs must be reported to the IEC and relevant Regulatory Authorities in a timely manner. Adequate documentation will be provided to the Sponsor, showing that the IEC and relevant Regulatory Authorities have been properly notified.

If required, a follow-up report including all new information obtained on the serious adverse event must be prepared and sent to the Monitor of the Sponsor. The report should be marked "Follow-up report".

The Investigator will submit, on request, copies of all these reports to the Independent Ethics Committee and other relevant authorities.

*Post-study events*

Any adverse event occurring at any time outside the observation period or after the end of the study and considered to be caused by the study vaccine - and therefore a possible adverse drug reaction - must be reported to the Sponsor.

- 1. Immunogenicity Assessments

At pre and post immunisation visits outpatient visits according to the schedule in Table1-3, the following samples will be obtained:

- 7 mL blood taken into plain tubes with gel for collection of serum.
- 35 mL blood taken into sodium heparin tubes for separation of PBMCs according to laboratory SOPs for cellular assays.

At each time point indicated on the schedule, vaginal and cervical secretions will be taken according to a predefined SOP, and aliquoted into cryovials before immediately freezing at ultra-low temperature. Cytobrush sampling will be performed as per Tables 1-3.

Assays will be performed in batches for each volunteer once their final visit has been completed.

## Total blood draw during the study

The total blood draw during the entire study will be of 502 ml.

# STATISTICAL CONSIDERATIONS

## Data Management and analysis

Data management will be in accordance with a pre-defined Statistical Analysis Plan and data management workflow agreed between the sponsor and a subcontractor prior to any evaluation of data.

## Sample Size

A sample size of 10 is regarded as sufficient to detect immediate reactogenicity and safety in Phase 1 clinical trials. All immunogenicity read-outs are exploratory, and as this is a hypothesis-generating study, no sample size calculation is practicable, but a study group of 20 is thought to be of sufficient size.

## Statistical Analysis Plan

A full SAP will be written by a subcontractor.

- - 1. Experimental Methods
       1. Study Design

This study will be a Phase I, randomised, two-centre, double-blind, hypothesis generating study to determine the reactogenicity and immunogenicity of vaginal immunisations with 9 applications of CN54gp140.

- - - 1. Subject Populations

(a) Universal population:

All subjects enrolled and allocated a group in the study. This population will be used for analysis of demographics and all subject listings.

(b) Safety population:

All subjects who receive a vaccination and with some follow-up safety data will be included for safety analysis. This population will be used for analysis of local and systemic adverse events.

(c) Intention to treat (ITT) population:

All subjects who receive a vaccination and who provide evaluable data before and after vaccination.

(d) Per-protocol (PP) population:

All subjects who receive a vaccination and who provide evaluable data before and after vaccination and with no major protocol violations. A "major" violation is defined as a protocol deviation that is considered to have an impact on the results of the study. The protocol deviations will be identified prior to the analysis (visit out of window, in-exclusion criteria, forbidden concomitant medications) and a clinical judgment will be necessary to classify each deviation as "major" or not.

- - 1. Data Analysis
       1. Background Characteristics

Descriptive statistics (mean, standard deviation, median, minimum and maximum) for age, height and weight at enrollment will be calculated overall and by treatment group.

Distributions of subjects by ethnic origin will be summarized overall and for each treatment group.

- - - 1. Statistical Analysis
         1. Primary Variables: Safety and Tolerability

##### Summaries presenting number of subjects reporting AEs will be prepared. The original verbatim terms used by the investigator to identify adverse events in the Case Report Forms (CRFs) will be mapped to preferred terms using MedDRA. The adverse events will then be grouped by preferred terms into frequency tables according to system-organ class (SOC). When an adverse event is reported more than once by the same subject, the maximal severity and causality will be counted. Adverse events that are considered to be possibly or probably related to study treatment will be summarized separately. Serious adverse events and adverse events leading to premature withdrawal from study will be listed. Additionally, adverse events that are unrelated to vaccine will be summarized and data listings of all adverse events will be provided. Summaries presenting number of subjects reporting local and systemic reactions will be prepared separately as a subset of all the AEs.

- - - - 1. Exploratory Variables: Immunogenicity

Individual values output from immunogenicity assays will be classified as ‘no response detected’ or ‘response detected’, according to predefined cut‑offs identified during assay validation. The results will be tabulated as appropriate. There will be no statistical analysis of exploratory variables. The Data Monitoring Committee will advise whether the overall level of immunogenicity warrants the completion of the planned recruitment or a premature termination of the study.

- - 1. Withdrawals

The number of subjects who withdraw and their reason for withdrawal will be listed and tabulated.

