| **STATISTICAL METHODS** | No statistical null hypothesis is formulated for this phase I study. This study is hypothesis generating.  Twenty and ten subjects in vaccine and gel only groups respectively are judged to be enough to obtain good estimates of safety and preliminary immunogenicity, to be possibly used in the design of later Phase 2a studies of immunogenicity.  Running analysis of immunogenicity data will be performed as subjects complete their final visit. An unblinded Data Monitoring Committee will evaluate immunology results. |

TABLE OF CONTENTS

[1 List of Abbreviations and Definitions of Terms 11](#__RefHeading___Toc160538478)

[2 INTRODUCTION 13](#__RefHeading___Toc160538479)

[2.1 Background 13](#__RefHeading___Toc160538480)

[2.2 Review of investigational medicinal product (IMP) 13](#__RefHeading___Toc160538481)

[2.3 Rationale for the trial 14](#__RefHeading___Toc160538482)

[2.4 Rationale for the choice of dose 14](#__RefHeading___Toc160538483)

[3 OBJECTIVES 15](#__RefHeading___Toc160538484)

[3.1 Primary Objective 15](#__RefHeading___Toc160538485)

[3.2 Exploratory Immunogenicity Objectives 15](#__RefHeading___Toc160538486)

[4 variables for assessment 15](#__RefHeading___Toc160538487)

[4.1 Primary Variables: Safety and tolerability 15](#__RefHeading___Toc160538488)

[4.2 Exploratory Variables: Immunogenicity 16](#__RefHeading___Toc160538489)

[5 Study DESIGN 16](#__RefHeading___Toc160538490)

[5.1 Allocation to treatment groups 16](#__RefHeading___Toc160538491)

[6 study population 16](#__RefHeading___Toc160538492)

[6.1 Number of Subjects 16](#__RefHeading___Toc160538493)

[6.2 Inclusion Criteria 17](#__RefHeading___Toc160538494)

[6.3 Exclusion Criteria 17](#__RefHeading___Toc160538495)

[6.4 Withdrawal of Subjects from the Study 18](#__RefHeading___Toc160538496)

[6.4.1 Interruption of dosing 18](#__RefHeading___Toc160538497)

[6.4.2 Discontinuation of dosing 18](#__RefHeading___Toc160538498)

[6.4.3 Withdrawal 19](#__RefHeading___Toc160538499)

[6.4.4 Policy for replacing withdrawals 19](#__RefHeading___Toc160538500)

[6.5 Criteria for Stopping Study 19](#__RefHeading___Toc160538501)

[7 STUDY MEDICATION 20](#__RefHeading___Toc160538502)

[7.1 Detail of Study Treatments 20](#__RefHeading___Toc160538503)

[7.2 Packaging and Labelling 20](#__RefHeading___Toc160538504)

[7.2.1 CN54gp140 protein 20](#__RefHeading___Toc160538505)

[7.2.2 Gel vehicle 21](#__RefHeading___Toc160538506)

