The vaccine formulation consists of CN54gp140 presented in an aqueous gel vehicle that contains ingredients used widely in vaginal products. The gel vehicle is suitable for self‑administration. A gel formulation is preferable to a liquid formulation because it will reduce leakage from the vagina in the period following administration. Such leakage is known to be a major barrier to user acceptance of vaginally delivered products.

Women appear to be disproportionately affected by HIV and, particularly in the developing world, may not be empowered to make sexual choices. Our approach utilizes a user-enabled technology that will be easy to use and cheap to manufacture for global use.

- 1. Rationale for the choice of dose

Each immunisation will contain 100µg CN54gp140 protein, meaning that a total dose of 900 µg will be given over nine immunisations.

We selected 100 µg CN54gp140 per immunisation to harmonise with ongoing clinical trials of closely related recombinant Env proteins. In one of those trials, ongoing at St George’s, University of London (EudraCT number 2005 005983 10), repeated immunisations of 100µg protein are being given via intranasal (IN) and intramuscular (IM) routes. In trials ongoing in the US, repeated immunisations of 100µg protein are via the IM route only. Judging by the preliminary data available, all immunisations with 100µg recombinant Env in these ongoing trials have so far been safe and well tolerated.

The selection of 100 µg per immunisation in the ongoing trials described above was based on dose‑ranging studies in preclinical animal models, including rodents, rabbits and non-human primates. The small differences between recombinant Env proteins used in different trials are not expected to cause significantly altered immunogenicity, so harmonizing to 100 µg protein per immunisation will enable a preliminary evaluation of intravaginal delivery versus IN and IM routes.

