## Exploratory Variables: Immunogenicity

1. A change from baseline in vaginal secretion IgA and IgG antibody responses against HIV-1 gp140.
2. A change from baseline in cervical secretion IgA and IgG antibody responses against HIV-1 gp140.
3. A change from baseline in serum IgG, IgA antibody responses against HIV-1 gp140.
4. A change from baseline in T-cell responses in blood to HIV-1 gp140.
5. A change from baseline in the frequency of cellular responses to gp140 in cervical cells after a cycle of 9 vaginal immunisations.

Immunogenicity assays will be conducted by St. Georges University of London Immunology Core Laboratory .

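### The protocol plans no summary of the size, spread or time course of the immune responses, although its exploratory variables are mostly defined as changes from baseline

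*Protocol*

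**What the plan says.** Section 9.3.2 (Exploratory Variables: Immunogenicity) fixes the scale of the read-out: "Individual values output from immunogenicity assays will be classified as ‘no response detected’ or ‘response detected", "according to predefined cut‑offs identified during assay validation". It continues "The results will be tabulated as appropriate" and then "There will be no statistical analysis of exploratory variables".

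Other sections bear on this:

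- **Section 3.2** words all four exploratory objectives as frequencies of response.
- **Section 4.2** words the variables as changes, for example "A change from baseline in serum IgG, IgA antibody responses against HIV-1 gp140" and "A change from baseline in T-cell responses in blood to HIV-1 gp140". Items 1 to 4 concern antibody or T-cell responses. Item 5 is a change in a frequency.
- **Synopsis, Statistical Methods** judges 20 and 10 subjects enough for good estimates of safety and of preliminary immunogenicity, "to be possibly used in the design of later Phase 2a studies of immunogenicity". It states no null hypothesis.
- **Section 2.4** says that using the same dose as related trials "will enable a preliminary evaluation of intravaginal delivery versus IN and IM routes".
- **Section 9.3.2 (Background Characteristics)** plans mean, SD, median, minimum and maximum for age, height and weight. No such summary is planned for any immune read-out.

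**The concern.** The assays produce individual values, and the only planned use of them is a two-level label. The label shows how many subjects crossed a cut-off. It does not show by how much, how variable the responses were, or how long they lasted over the post-immunisation visits.

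Two stated uses would benefit from that information. A Phase 2a study with a quantitative endpoint needs a mean and an SD for its sample size. A comparison with the intranasal and intramuscular routes is thin on responder rates alone, because routes with similar rates can differ in level.

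This is not a detail left to the SAP. The protocol itself sets the classification and excludes statistical analysis, so a SAP that added estimates and intervals would sit badly with the protocol.

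**Working it through.** **No figure to reproduce.** Section 9.2 says no sample size calculation is practicable. The protocol gives no SD, effect size, alpha, power or cut-off value.

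**1. What is defined against what is summarised**

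| Source | What it asks for | Served by the responder table? |
|---|---|---|
| 3.2, objectives 1–4 | Frequency of response | Yes, but no interval is planned |
| 4.2, items 1–4 | Change from baseline in response | No |
| 4.2, item 5 | Change in a frequency | In part |
| Synopsis | Estimates of preliminary immunogenicity | Proportion only; no mean or SD |
| 2.4 | Preliminary route evaluation | Rates only |

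**2. Precision available from 20 vaccinated subjects**

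- Responder proportion, exact (Clopper-Pearson) 95% CI: 5/20 gives 8.7% to 49.1%. For 0/20 the upper limit is 1 − 0.025^(1/20) = 16.8%.
- SD of a log value: multiplier √(19/χ²) at the 97.5th and 2.5th percentiles, ×0.76 to ×1.46.
- Mean: ± t(0.975, 19)/√20 = 2.093/4.472 = ±0.47 SD.

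The planned table gives the proportion without an interval, and neither of the other two.

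**3. Illustration of the information lost by cutting**

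Assumptions, none from the protocol: normal log values, equal SD, two-sided 5%, and a cut-off at the placebo 95th percentile (1.645 SD above the placebo mean). Group sizes of 20 and 10 are from the synopsis.

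*Uniform shift of 1.0 SD*

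- Vaccine responders: 1 − Φ(1.645 − 1.0) = 26%. Placebo: 5%.
- Classified values: summing the binomial probabilities of all tables with Fisher exact p ≤ 0.05 gives power **8%**.
- Full scale: t-test with noncentrality 1.0/√(1/20 + 1/10) = 2.58, 28 df, critical value 2.048, gives power **70%**. Simulated Wilcoxon gives 65%.
- Randomised subjects only (19 v 10): 6% v 69%.

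*Sensitivity to the shift and the cut-off*

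- At 1.0 SD, the most favourable cut-off tried (the placebo mean) gives 45% v 70%.
- At 1.5 SD, with the 95th-percentile cut-off, 56% v 96%.
- At 0.5 SD even the full-scale t-test has only 24%.

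*All-or-none responses: a fraction of vaccinees jumps 3 SD, the rest do not move*

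- 50% responding: proportion above the cut-off 0.5 × 0.912 + 0.5 × 0.05 = 48%. Fisher **66%** v Wilcoxon **59%**.
- 30% responding: 0.3 × 0.912 + 0.7 × 0.05 = 31%. Fisher 17% v Wilcoxon 21%.

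So the loss is large for a shift shared by all subjects. It is small or reversed, against the rank test, when a few subjects respond strongly.

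**The case against.** The strongest reply is that the read-out matches the objectives: all four ask for a frequency, and a responder table gives one. That stands, and is why the responder rate should stay. A responder proportion can also drive a Phase 2a sample size if response rate is the endpoint, and the synopsis claims only a possible use.

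A second reply is that tabulation as appropriate leaves room for descriptive tables. This is arguable. But the phrase follows directly on the classification, and the next sentence excludes statistical analysis. At best the text is ambiguous about summaries, and an estimated difference with a confidence interval is hard to fit within it.

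A third reply is that the power figures compare tests that the plan will not run, on assumed distributions. This also stands: they illustrate loss of information and do not measure a fault in a planned test.

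A reader might infer more than the documents support:

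- *That the values are discarded.* They are generated, and the subject listings foreseen in section 9.3.1 could show them. What is missing is a planned summary.
- *That the Data Monitoring Committee sees only a yes/no table.* The synopsis and section 6.5 have it review immunogenicity results, and section 9.3.2 has it advise on the overall level of immunogenicity. None of these limits the form of the data.
- *That weak responses are to be expected, so the cut-off will hide them.* Nothing in the protocol says so. Section 2.4 reports a specific antibody response in rabbit serum and vaginal secretions under the same regimen.

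**Conclusion.** The point holds as a gap between what the protocol defines and what it plans to summarise. The two-level classification serves the objectives in section 3.2. It leaves items 1 to 4 of section 4.2 without any summary of change, and it gives no size, spread or time course for the uses named in the synopsis and section 2.4.

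The practical size cannot be fixed from the protocol. The 8% v 70% contrast rests on an assumed uniform normal shift and an assumed cut-off. It largely vanishes or reverses if responses are all-or-none, and would also be small if most values lay below the detection limit. It is therefore not shown that modest shifts will be missed. The case for change rests on the missing description and does not depend on the power figures.

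Only exploratory read-outs are affected. The change is worth making because it costs almost nothing.

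**What to change.** In section 9.3.2, keep the responder frequency and add an exact 95% CI by group. Replace "There will be no statistical analysis of exploratory variables" with wording such as:

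> No formal hypothesis testing. For each quantitative assay and compartment, the log10 value and the log10 change from the pre-immunisation value will be summarised by group and post-immunisation visit (geometric mean, SD, median, range), with the vaccine-minus-placebo difference and 95% CI (rank-based or censored-data method where values lie below the detection limit). These summaries are descriptive and unadjusted for multiplicity.

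The text should also name the pre-immunisation visit used as reference, since Tables 1–3 schedule secretion samples at both visit 1 and visit 2.

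The cost is a few extra tables from values already produced, with no added samples, visits or assays. With many assays, compartments and visits, some intervals will exclude zero by chance, which is why the descriptive label matters.

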# Quality Assurance Procedure

The St George’s Vaccine Institute and York Hospital Department of GU Medicine will conduct all study procedures in accordance with the appropriate regulatory requirements and their Standard Operating Procedures. A clinical research organisation will be subcontracted to perform independent auditing and monitoring.

# Investigator responsibilities

The Sponsor will be responsible for pharmacovigilance, monitoring, data monitoring, organising GCP audits and managing inspections by the regulatory agencies.

## Investigator Performance

All clinical work conducted under this protocol is subject to GCP rules. This may include an inspection by the Sponsor and/or Health Authority representatives at any time. The Investigator must agree to the inspection of study-related records by the Regulatory Authority representatives.

The Investigator must adhere to the following principles in addition to any applicable local regulations. The Investigator will also ensure that all staff involved in the conduct of the study are provided with copies of the protocol and all safety information before study start and are fully familiar with their role.

## Ethical Considerations

- - 1. Independent Ethics Committee

This protocol, informed consent document, and any other written information to be provided to subjects other than general non-specific information, must have the written, dated approval of a properly constituted Independent Ethics Committee (IEC).

Any substantial amendments must be submitted to the IEC and/or the appropriate national Regulatory Authority. A favourable opinion from IEC and/or a notice of no objection from the appropriate national Regulatory Authority is required prior to their implementation, unless the amendment is to reduce immediate hazard to study subjects.

A copy of the dated, written approval of the amendments must be provided to the Sponsor.

Changes involving only logistical or administrative aspects of the study (non substantial amendments) need not be submitted to the IEC for approval.

The Sponsor should keep a record of such amendments that must be made available to the appropriate national regulatory authority and/or IEC on request.

The Principal Investigator should supply the Sponsor with:

- the names and qualifications of IEC members present at the study protocol review meeting (main Ethics committee in London, site-specific in York).
- a statement from the IEC that it is organised and operates according to ICH GCP8, and applicable laws and regulations.
- documentation and dates of any IEC re‑approvals/re-evaluations, and of any withdrawals or suspensions of approval.
  - 1. Volunteer Informed Consent

Prior to the commencement of the study, each subject will be provided with written information giving details of the investigational product, procedures and potential risks involved during the study. Subjects will also be instructed that they are free to obtain further information from the Principal Investigator and that they are free to withdraw their consent and to discontinue their participation in the study at any time. At the same time, the subjects will be informed about the existence of an indemnification procedure.

All subject names will be filed confidentially in the Principal Investigator's files. Subjects will be identified in documentation and throughout evaluation by the study-specific subject number allocated to them on admission. The subjects will be told that all study findings will be stored on computer and handled in the strictest confidence.

Following discussion of the study with appropriate site staff, subjects will sign the study‑specific consent form, in the presence of a relevant site staff witness, to indicate that they are freely giving their informed consent.

Ongoing volunteers at the date of the implementation of this version of the protocol will be given a new version of the Information Sheet and will be asked to sign the new consent form. From the date of their signature, they will be included in the updated protocol.

- - 1. Ethical Conduct of the Study

The study will be performed in accordance with the Declaration of Helsinki (Hong Kong 1989, Somerset West 1996), Good Clinical Practice on Medicinal Products in the European Community (111/3976/88-EN - July 1990) and the Standard Operating Procedures of the Clinical sites and contractors.

- - 1. Information for Subject’s General Practitioner

As part of the informed consent process subjects will be required to consent to the notification of the General Practitioner with whom they are registered of her intended involvement in the study prior to commencement of the study. The GP will be asked to notify the Principal Investigator if they are aware of any contraindication to her participation.

- - 1. Payment to Subjects

All volunteers will be paid expenses and compensation for their inconvenience. The amounts to be paid will follow the standard rates submitted to the local IEC.

